## Statistical Methods

Basic demographic data will be retained on the anticipated small number of excluded patients as these form part of the at risk population. Descriptive statistics will be used to provide a summary of each of the variables collected at each time point. Multivariable linear regression analysis will be used to assess the effect of baseline variables as well as changes in these variables over the first 12 months on changes in blood pressure, proteinuria and glomerular filtration rate. Cox proportional hazards models will be used to identify independent baseline risk factors for CKD progression and cardiovascular events at 5 and 10 years. A similar method will be used to assess the possibility that changes in baseline variables from baseline to 12 or 24 months may be better predictors of CKD progression and cardiovascular events than baseline variables alone. Coefficients derived from Cox proportional hazards analysis for the independent determinants of CKD progression or cardiovascular events will then be used to produce a risk scoring system.

In a subgroup of 160 patients, assessment of proteinuria by urine protein to creatinine ratio versus albumin to creatinine ratio or 24h urinary protein will be assessed. Intraclass Correlation Coefficients will be used for comparing the three methods and Bland-Altman plots will be performed. 24 hour urinary protein will be the standard against which the other methods are compared. Similar analysis will be performed to compare urinary sodium and phosphate assays in spot and 24 hour urine specimens.

Estimated GFR values obtained with a new creatinine-cystatin-C equation [12] will be compared to eGFR derived from creatinine alone using a paired t-test to compare the mean values and by Bland-Altman plots. The intraclass correlation coefficients (95% Confidence Interval) will be used to check the agreement of eGFR estimates by different equations. The analysis will be repeated in clinically important subgroups including participants under 75 years versus 75 years or older, males versus females and those with diabetes versus those without. The change in eGFR over 5 years determined by each of the GFR estimating equations will be similarly compared. We will compare the performance of prognostic models using eGFR derived from creatinine versus combined creatinine-cystatin-C equation with respect to discrimination (C-statistic derived from ROC curves) and calibration (Hosmer Lemeshow test, net reclassification index (NRI)). We will repeat these analyses using change in GFR (estimated from creatinine or combined equations) and albuminuria over the first year of follow-up as independent variables as well as baseline values to test whether change over the first year adds to the prognostic model.

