**Study Centres**

Royal Derby Hospital

GP Practices within Southern Derbyshire CCG, North Derbyshire CCG

and Erewash CCG.

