## To assess the management of patients with CKD stage 3 by General Practitioners compared with Renal Association Clinical Practice Guidelines.

## To develop care plans to improve the care of patients with CKD stage 3 within Primary Care.

## To assess the value of monitoring urine albumin to creatinine ratio (UACR), urine sodium and urine phosphate in the management of patients with CKD stage 3.

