## Subject Recruitment and Screening

Patients with CKD stage 3 (as defined above) will be identified from General Practice CKD registers and biochemistry databases by participating General Practitioners. GPs will send out the patient information sheet and a letter of invitation to potential participants. Patients will be invited to set up an appointment for the initial assessment by telephoning a number at Royal Derby Hospital. If patients do not wish to participate they will be asked to confirm this by telephoning the same number. If no response has been received within 2 weeks a second letter may be sent.

Informed consent to participate in the study will be obtained at the time of the first visit by the researchers, this will include consent to certain identifiable information being passed on to the Medical Research Information Service. Patients will have at least 1 week to decide about participation.

No additional screening procedures will be required prior to entry.

Each patient will be assigned a unique study number that will be used to identify all data collected for the study. This will be allocated at the first study visit. A key of patient identity and study numbers will be kept on a password-protected Trust computer in a password-protected file. Any information passed onto the Medical Research Information Service will be in encrypted form.

A recruitment log will be maintained.

Details of participation in the study will be recorded in the patients’ GP records.

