# Study Procedures

- Patients will be asked to complete an information sheet to provide demographic and medical history details prior to attending for the first study assessment. They will also be asked to complete a brief food frequency questionnaire to assess salt intake. Demographic and medical history will be assessed only at baseline. Current medication will be assessed at each study visit. The food frequency questionnaire will be repeated at each study visit. Medical history and treatment details will be checked against the GP records. If known, the cause of the CKD will be recorded and assigned a corresponding European Dialysis and Transplantation Association diagnostic code.
- The first part of the assessment (5-10 minutes) will comprise a patient interview to clarify details and complete any unfilled sections on the information sheet and food frequency questionnaire.
- A measure of socio-economic status with be derived from participants’ post code (Indicies of Multiple Deprivation(IMD) score)
- Quality of life will be assessed using the EQ5D questionnaire
- Functional status will be graded using the Karnofsky score
- Anthropomorphic Measurements (repeated at each study visit)
  - Height
  - Weight
  - Body Mass Index
  - Hip to waist ratio
  - Mid-upper arm muscle circumference
  - Hand grip strength
  - Gait speed
  - Sit to stand test
  - Blood pressure (seated; average of 3 readings recorded with an oscillometric device)
  - Peridontal assessment
  - Urine dipstick test
  - Non-invasive assessment of arterial pulsewave velocity (Viacorder, Skidmore Medical Ltd, Bristol, UK)
  - Non-invasive measurement of forearm skin autofluoresence as a measure of advanced glycation end product deposition (AGE Reader, DiagnOptics, Groningen, Netherlands)
- Venesection (repeated at each study visit)
  - 3 x 5ml clotted blood
  - 1x 3ml blood in EDTA
- Urine collection (repeated at each study visit)
  - 3 x 5-10ml first morning urine specimen

Each study visit is expected to last 30-40 minutes.

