## Sample Size Determination

The sample size was estimated based on two similar studies, one for predicting renal outcome in IgA nephropathy [4] and the other in patients with type 2 diabetes and nephropathy [3]. Based on these studies the smaller event rate was 12% and the smallest significant Hazard Ratio was 1.2. Therefore the total sample size for this study, using the Cox Proportional Hazards models with Power 80% and at significant level 5%, is 1968. Assuming death rate during the 5 years of 3% and drop out rate of 10% the final total sample is 2255. We plan to complete recruitment in 1 year and therefore aim to recruit approximately 190 participants per month. CKD stage 3 is estimated to affect at least 5% of the UK population. There should therefore be approximately 35,000 patients available for recruitment in Derbyshire.

A separate sample size estimate was performed for the sub-study comparing spot early morning urine biochemistry with that from 24hour urine collections. Based on previously published data, we calculated that a sample of 160 would allow us to show a correlation co-efficient of 0.9 with precision of the estimate of 0.03 at 80% power with a significance of 5% [7].

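### Participants are recruited through GP practices, but the sample size assumes independence and the Cox and linear models make no allowance for practice, so standard errors may be too small for covariates that partly cluster by practice

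*Protocol*

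**What the plan says.** **Recruitment.** The Study Summary lists as centres one hospital and "GP Practices within Southern Derbyshire CCG, North Derbyshire CCG" and a third CCG. Section 4.2 says that patients "will be identified from General Practice CKD registers and biochemistry databases by participating General Practitioners", and the GPs send the invitations. The number of practices is not given.

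**Analysis.** Section 8.2 says that "Cox proportional hazards models will be used to identify independent baseline risk factors for CKD progression and cardiovascular events at 5 and 10 years". It also plans multivariable linear regression for changes in blood pressure, proteinuria and GFR. Coefficients from the Cox models are then to form a risk score. Nothing in section 8 refers to practice, random effects, frailty or robust variance.

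**Sample size.** Section 8.1 takes it that "the smaller event rate was 12% and the smallest significant Hazard Ratio was 1.2". It concludes that the total, "using the Cox Proportional Hazards models with Power 80% and at significant level 5%, is 1968". It then adds: "Assuming death rate during the 5 years of 3% and drop out rate of 10% the final total sample is 2255". These are the only two inflations. The Study Summary gives 1822 as the number of subjects.

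**Covariates.** Section 7 states: "A measure of socio-economic status with be derived from" each participant's post code. Section 4.4 records current medication and past use of three drug classes, patient by patient.

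**The concern.** Patients of one practice share prescribers and, to a large extent, a neighbourhood. If both a covariate and the outcome are more alike within practices than between them, the usual model-based variance understates the uncertainty of that covariate's coefficient. Deprivation scores and GP-prescribed treatment are plausible examples. A creatinine, cystatin C or grip-strength value, which varies mainly between individuals, is much less exposed.

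The stake is the list of risk factors called independent and the score built from it. If entry to the score depends on significance (section 8.2 does not give the selection rule), a covariate that tracks practice could enter more often by chance than the nominal 5% implies, and its interval would be too narrow.

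**Working it through.** **Step 1: reproduce the plan's figure.** Inputs from section 8.1: two-sided 5% (sidedness is not stated, but two-sided reproduces the result), power 80%, hazard ratio 1.2, event rate 12%. For a standardised covariate (variance 1, inferred because it reproduces the result):

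- Events = (1.960 + 0.842)² / (ln 1.2)² = 236.1
- N = 236.1 / 0.12 = 1967.7, which rounds up to 1968
- Inflated N = 1968 / (0.97 × 0.90) = 2254.3, which rounds up to 2255

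Both stated figures are met exactly with a design effect of 1. Independence in section 8.1 is therefore shown by calculation. It is not inferred from silence.

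**Step 2: effect on a test.** For a regression coefficient, with m patients per practice, the approximate design effect is

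DE = 1 + (m − 1) × ICC of covariate × ICC of outcome,

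and the true error rate of a nominal 5% test that ignores practice is 2 × (1 − Φ(1.96 / √DE)).

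**Step 3: inputs that the documents do not give.** These are assumptions: 32 practices, so m = 1822 / 32 ≈ 57; outcome ICC 0.01 to 0.05; covariate ICC as shown.

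| Covariate ICC | Outcome ICC 0.01: DE, true error | Outcome ICC 0.05: DE, true error |
|---|---|---|
| 0.05 (weak clustering) | 1.03, 5.3% | 1.14, 6.6% |
| 0.3 (partial clustering) | 1.17, 7.0% | 1.84, 14.8% |
| 1 (constant within practice) | 1.56, 11.7% | 3.80, 31.5% |

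For the middle row: 1 + 56 × 0.3 × 0.01 = 1.168 and 1 + 56 × 0.3 × 0.05 = 1.84. The square roots are 1.08 and 1.36, so the true standard error is about 8% or 36% larger than the one reported. The last row is a bound only: no covariate that the protocol lists is constant within a practice.

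**Step 4: check by simulation.** Cohorts of 1822 with 12% events, a practice effect on the hazard and a null covariate were fitted with a one-covariate Cox model, 1500 per setting. At m ≈ 57 and covariate ICC 0.3, the false-positive rate was 6.9% at outcome ICC 0.01 and 14.7% at 0.05. At outcome ICC 0.05 and covariate ICC 0.3, it was 9.9% with 30 patients per practice and 19.7% with 90.

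**Step 5: does clustered variance help?** In the setting with 32 practices, outcome ICC 0.05 and covariate ICC 0.3, plain practice-clustered variance brought the rate from 14.7% to 7.8%. The remaining excess over 5% is the reason for a small-sample correction.

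**The case against.** The strongest reply is that section 8.2 gives each model one sentence and never says that participants will be treated as independent; the word independent there describes risk factors. A variance estimator is often left to a statistical analysis plan, and none is shown. This has force: for section 8.2 the naive variance is only the natural reading of the models as named. But section 8.1 does assume independence, and nothing in 8.2 departs from it. The point therefore stands as a cheap improvement to a model specification, and it does not show an error already made.

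Three further points stand and limit the size. The deprivation score comes from each participant's own post code and treatment is recorded per patient, so clustering by practice is only partial. The protocol does not say which covariates enter the Cox models. The simulation used a single covariate, whereas adjustment for patient-level predictors may absorb some between-practice variation and lower the inflation.

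A reader might also infer that percentages of patients managed to guideline would carry intervals that are too narrow, because section 2 includes the objective "To assess the management of patients with CKD stage 3 by General Practitioners compared with Renal Association Clinical Practice Guidelines". The protocol does not support that: section 8.2 assigns this objective no model, percentage or interval, so there is no stated analysis to criticise.

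A shared frailty for practice may look like an equivalent remedy. It would make hazard ratios conditional on practice, which complicates a score meant for patients elsewhere, so it is not proposed here.

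**Conclusion.** The concern holds in a limited form. Recruitment is through practices, the sample size assumes independent participants, and the named models make no allowance for practice. If they are run as written, standard errors may be too small for covariates that partly cluster by practice, while most patient-level biomarkers are barely affected.

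On assumed values (about 57 per practice, covariate ICC 0.3), the nominal 5% becomes about 7% to 15% as the outcome ICC goes from 0.01 to 0.05. A reader might infer that all p-values and intervals are wrong, or take the practice-level figure of about 32% as the expected error. Neither follows: the number of practices and both ICCs are unknown, and no listed covariate is purely practice-level. The gap between 1822 and 2255 is a separate matter and is not part of this point.

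**What to change.** In section 8.2, state that the GP practice of each participant is recorded, and that the Cox and linear models use variance clustered on practice, with a small-sample correction if practices are few (fewer than about 40, say). Report the number of practices.

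For a given set of covariates, the coefficients and the risk score do not change. The cost is a sentence of text and slightly wider intervals for practice-related covariates. No new patients are needed, and practice should be known from recruitment, since GPs identify and invite the patients and participation is noted in GP records.

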## To assess associations between CKD and a wide range of previously described risk factors.

# Study Design

## General Design

This is a long-term longitudinal observational cohort study.

Patients will be followed for 10 years. Clinical assessments will take place as described at baseline, 1 year and 5 years. After this patients will no longer be assessed clinically but outcome data with respect to the primary end points as well as survival will be collected. The Medical Research Information Service (MRIS) will (an arm of the NHS Information Centre), will be used to accurately track survival data of participants.

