# Laboratory Assays

The following laboratory tests will be obtained at baseline, 1 year and 5 years. The majority of these tests form part of routine clinical care and would normally be performed annually by the General Practitioner. Tests marked with an asterix are not routine and will be performed by the researcher in a research laboratory. Participants will be asked not to eat meat for 12 hours prior to the blood tests (to avoid a potential effect on the creatinine assay).

- Urea and electrolytes
- Estimated GFR
- Calcium and phosphate
- Serum albumin
- Lipid profile
- Random blood glucose
- Bicarbonate
- Uric acid
- Full blood count
- Urine albumin:creatinine ratio (on three early morning specimens)
- Urine protein:creatinine ratio (on three early morning specimens)
- Urine sodium (on three early morning specimens)
- Urine phosphate (on three early morning specimens)
- 24h urine collection for measurement of urinary creatinine, protein, albumin, sodium and phosphate will be performed in a subgroup of 160 patients.
- High sensitivity C-reactive protein (CRP)
- ADMA (asymmetrical dimethyl arginine)
- Serum fibroblast growth factor 23 (FGF 23)*
- Serum 25 hydroxy-vitamin D
- Serum 1,25 dihydroxy-vitamin D
- Serum Parathyroid hormone
- Serum Cystatin C
- Serum free light chains
- Serum will be stored for future biochemical assays but these will not include genetic testing. This to allow testing of substances that may be identified as significant risk factors for renal or cardiovascular outcomes during the follow-up period. Serum will not be stored beyond the duration of the study.

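### The risk score takes its weights from whichever variables survive Cox selection, with no shrinkage or optimism correction, so it is likely to overstate differences in risk between patients

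*Protocol*

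**What the plan says.** Protocol section 8.2 sets out two steps. First, "Cox proportional hazards models will be used to identify independent baseline risk factors for CKD progression and cardiovascular events at 5 and 10 years". Second, "Coefficients derived from Cox proportional hazards analysis for the independent determinants of CKD progression or cardiovascular events will then be used to produce" the score. A similar approach is then applied to changes in the variables over the first 12 or 24 months.

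The protocol names no restricted list of candidates. One of its objectives (section 2) is "To assess associations between CKD and a wide range of previously described risk factors". Section 5 lists the laboratory measurements ("The following laboratory tests will be obtained at baseline, 1 year and 5 years"), and section 7 lists the questionnaires and physical measurements.

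The only significance level given for the Cox models is in section 8.1, where the sample size, "using the Cox Proportional Hazards models with Power 80% and at significant level 5%, is 1968". Its basis is that "the smaller event rate was 12% and the smallest significant Hazard Ratio was 1.2".

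Section 8.2 also mentions the C-statistic, the Hosmer-Lemeshow test and net reclassification. They are there to compare prognostic models that use different eGFR equations, and to test whether first-year change adds to those models. They are not applied to the coefficients of the score.

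**The concern.** When the same data choose the variables and supply their weights, two things go wrong together. Some variables with no real effect are kept by chance. Those that are kept, real or not, tend to have estimates that were large in this sample. A score built directly from those estimates spreads patients too widely: in new patients, those scored as high risk do less badly than predicted, and those scored as low risk do less well.

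This matters here because the Background presents prediction in individual patients as the gap to be filled, and criticises earlier scores for lack of validation in general CKD populations. Measures of discrimination and calibration computed afterwards can reveal the overstatement but do not remove it from the coefficients.

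**Working it through.** **1. The plan's own figure.** Inputs from section 8.1: hazard ratio 1.2, event rate 12%, power 80%, level 5% (two-sided reproduces the result).

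- Events = (1.960 + 0.842)² / (ln 1.2)² = 7.849 / 0.03324 = 236.1
- N = 236.1 / 0.12 = 1967.7, so 1968, as stated
- Inflation: 1968 / (0.97 × 0.90) = 2254.3, so 2255, as stated

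The sample size is correct for one covariate, with the hazard ratio read per standard deviation. It makes no allowance for choosing among many.

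**2. Candidates and events.** Section 5 has 21 blood and urine entries, leaving out the 24-hour subgroup and stored serum (22 if calcium and phosphate are counted separately). Section 7 has 17: the salt questionnaire, deprivation score, EQ5D, Karnofsky and 13 physical measures. Total: 38 or 39. Age, sex, history, medication, cause of CKD and first-year changes would add to this. Some entries overlap (height, weight, BMI); others are panels. I use 40.

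Events at the 1822 subjects in the Study Summary: 1822 × 0.12 = 218.6, about 219. Per candidate: 219 / 40 = 5.5.

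**3. Noise variables expected at 5%.** If 6 of 40 candidates are real, 34 are noise, and 34 × 0.05 = 1.7 are kept on average.

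**4. Benchmark if nothing predicts.** P(at least one kept) = 1 − 0.95^k: 40% at k = 10, 64% at k = 20, 87% at k = 40.

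**5. Size of the overstatement.** Simulation of the rule with 40 candidates, backward elimination at 5% and about 219 events. The slope is that of true on predicted log hazard in new patients; 1 is ideal.

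| True predictors assumed (HR per SD) | Noise variables kept | Slope |
|---|---|---|
| 4–10 at HR 1.2, normal approximation, correlation 0 or 0.5 | 1.5–2.3 | 0.61–0.75 |
| 6 at HR 1.2, full Cox model | – | 0.69 |
| 8 at HR 1.2, full Cox model, all correlations 0.2 | 1.6–1.9 | 0.85–0.86 |
| HR 1.2, further full Cox runs | at least one in 82–92% of runs* | 0.66–0.84 |
| 4–6 at HR 1.5, normal approximation | 1.7–1.9 | 0.92–0.94 |
| 5 at HR 1.5, full Cox model | * | 0.95 |

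*The 82–92% covers these two rows together.

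Part of the difference between rows lies in how widely true risk varies. With 6 uncorrelated predictors at 1.2, the SD of the true log hazard is √(6 × 0.03324) = 0.45. With 8 at correlation 0.2 it is √(0.03324 × (8 + 56 × 0.2)) = 0.80. More true spread means relatively less exaggeration. Varying the events from 191 (1822 × 0.873 × 0.12) to 271 (2255 × 0.12) in the normal-approximation runs gave slopes of 0.57 to 0.95, always below 1.

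**6. What a slope means.** Suppose the score says that two patients differ by a hazard ratio of 3. The ratio in new patients would be 3^0.6 = 1.9 at slope 0.6, 3^0.85 = 2.5 at slope 0.85, and 3^0.95 = 2.8 at slope 0.95.

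**The case against.** The strongest objection is that much of the rule tested above is supplied, not quoted. Section 8.2 gives no threshold, no stepwise procedure and no candidate list. The 5% comes from the sample-size section, and backward elimination was chosen for the simulation. Sections 5 and 7 are lists of what is collected, which also serve the descriptive and care-audit objectives. A separate analysis plan, not at hand, could add a threshold, shrinkage or validation. All of this stands as a limit on the size of the problem. It does not remove the problem: the protocol itself states that selected variables contribute their Cox coefficients to the score, so this is a stated method and not only missing detail.

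A reader might infer from the 87% benchmark that the score will almost certainly be spurious. The documents do not support that. The candidates are described as previously reported risk factors, so a complete absence of effects is implausible, and the figure falls to 40% with 10 candidates.

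A reader might also infer that formal false-discovery control is required for the risk-factor aim. In an observational risk-factor study that is a debatable preference, not the correction of an error.

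Nor does the point show a wrong sample size; 1968 and 2255 both reproduce.

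**Conclusion.** The concern holds in a limited form. The protocol fixes a way of building the score that selects variables and then uses their coefficients without shrinkage or optimism correction. With roughly 40 measurements available and about 219 events, that overstates differences in risk in every setting examined.

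About 2 noise variables are typically kept. The slope in new patients is about 0.6 to 0.85 if true hazard ratios are near 1.2, and about 0.92 to 0.95 if predictors are strong, in which case the practical harm is small.

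These sizes rest on two assumptions that the protocol does not state: selection at 5%, and most of the collected measurements being candidates. They also depend on the assumed effect sizes and correlations. A short candidate list or a few dominant predictors would make the problem milder.

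**What to change.** In section 8.2, replace the sentence on how the score is produced. Either of these would do:

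- *Penalised model.* Derive the score for each endpoint from a candidate list fixed before outcome data are examined, using a Cox model with a lasso or elastic-net penalty chosen by cross-validation. The penalised coefficients form the score.
- *Selection with correction.* Fix the candidate list in the same way and state the selection rule. Repeat the whole selection and fitting in bootstrap samples, shrink the coefficients by the estimated optimism, and report optimism-corrected discrimination and calibration.

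A ridge penalty alone is not proposed. In simulation it brought the slope to 1.03 at 12% events, which shows that shrinkage addresses the fault. But it drops no variable, so every research assay would have to be measured to use the score, which suits primary care poorly. At an assumed 5% event rate it also over-shrank (slope 1.33). The two options above were not themselves simulated.

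Cost: somewhat more analysis, smaller coefficients, and no simple confidence intervals for penalised coefficients. No new data, visits or patients are needed.

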## Background

The introduction of estimated glomerular filtration rate (GFR) to assess renal function has identified large numbers of patients with previously undetected chronic kidney disease (CKD). It is clear from previous studies that there is considerable heterogeneity in the risk of decline in renal function among patients with similar levels of GFR. Patients therefore differ widely in their need for specialist referral and treatment. Epidemiological studies have identified multiple risk factors for CKD progression [1] but few have sought to define the risk in individual patients. Several attempts have been made to develop scoring systems to predict renal risk but these studies have largely been limited to patients with specific kidney diseases and have not been validated in more general populations of patients with CKD [2-4]. Chronic kidney disease is also associated with an increased risk of cardiovascular disease that in many cases’ exceeds the risk of developing end-stage renal disease (ESRD) [5]. It is not known, however, whether traditional cardiovascular risk factors are relevant in patients with CKD or whether cardiovascular risk assessment tools used in the general population are applicable to patients with CKD. Recent data indicates that the extent of advanced glycation end product (AGE) deposition in the skin is an important marker of cardiovascular risk among patients with CKD [6] and periodontal status has also been associated with risk of cardiovascular disease in those with and without CKD [7-10]. Preliminary data suggest that cardiovascular disease may also be a risk factor for CKD progression. Thus kidney and cardiovascular disease may exacerbate each other, leading to a vicious circle of progressive cardiovascular and renal decline.

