## Subject Population(s) for Analysis

All patients will be included in the analyses described above except for the analyses that include results derived from 24 hour urine collections (subgroup of 160 patients only). Data from patients who withdraw (and give consent) or who die will be included until the date of withdrawal or death. Analyses of data from 24 hour urine collections will be applied only to the relevant subgroup.

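### The Cox models behind the risk score censor deaths, so absolute 5- and 10-year risks read from them will be somewhat too high, chiefly for the renal endpoint

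*Protocol*

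**What the plan says.** Section 8.2 (Statistical Methods) states that "Cox proportional hazards models will be used to identify independent baseline risk factors for CKD progression and cardiovascular events at 5 and 10 years". The coefficients "for the independent determinants of CKD progression or cardiovascular events will then be used to produce a risk scoring system". Later in the same section, prognostic models are to be compared on discrimination and on calibration, the latter by a Hosmer-Lemeshow test.

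Section 8.3 (Subject Population(s) for Analysis) gives the rule for deaths: "Data from patients who withdraw (and give consent) or who die will be included until the date of withdrawal or death". Death and withdrawal are handled alike. In a Cox model that amounts to censoring at the date of death.

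Section 3.2 defines the renal endpoint as doubling of creatinine or need for renal replacement therapy, so death is not a component. The cardiovascular endpoint does include some deaths: fatal myocardial infarction, fatal stroke, death from peripheral vascular disease and sudden cardiac death.

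The only mortality figure is in section 8.1: "Assuming death rate during the 5 years of 3% and drop out rate of 10% the final total sample is 2255". The protocol gives no death rate at 10 years and none by age.

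**The concern.** Censoring is a fair description of a patient who leaves observation but could still have the event later. It does not describe a patient who has died. A Cox model that censors deaths estimates the cause-specific hazard: the event rate among those still alive and event-free. Turning that hazard alone into a probability, as one minus the event-free survival curve, gives the risk in a setting where nobody dies first. That is always at least as large as the proportion of patients who will actually have the event.

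The first two objectives in section 2 are to define the risk of kidney function decline and of cardiovascular disease. A score giving 5- or 10-year probabilities would be the main product of that work. If it ignores competing deaths, its stated risks are too high, and the error grows with the length of the horizon and with the death rate of the patients to whom it is applied.

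**Working it through.** **The plan's own figures.** Section 8.1 gives an event rate ("the smaller event rate was 12" per cent), a hazard ratio ("the smallest significant Hazard Ratio was 1.2"), 80% power and a 5% significance level. Taking the hazard ratio per standard deviation of a continuous covariate and a two-sided test:

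- Events = (1.960 + 0.842)² / (ln 1.2)² = 236.1.
- N = 236.1 / 0.12 = 1967.7, so 1968, as stated.
- Allowing for 3% deaths and 10% dropout: 1968 / (0.97 × 0.90) = 2254.3, so 2255, as stated.

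The 3% and 12% are therefore working inputs of the plan, and I use them as the base case.

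**Inputs for the check.**

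- F1, event risk by 5 years: 12% (section 8.1, read here as a 5-year figure).
- F2, deaths without the event by 5 years: 3% (section 8.1, with all deaths taken as competing, as suits the renal endpoint).
- Other values of F2 are my assumptions.
- Hazards are constant.

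**Formulas.**

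- Total hazard: H = −ln(1 − F1 − F2) / 5.
- Event hazard: h1 = H × F1 / (F1 + F2). Death hazard: h2 = H × F2 / (F1 + F2).
- Risk at time t with deaths censored: 1 − exp(−h1 t).
- Actual risk (cumulative incidence): [h1 / (h1 + h2)] × [1 − exp(−(h1 + h2) t)].

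**Base case, 3% deaths.** H = −ln(0.85) / 5 = 0.03250 and h1 = 0.03250 × 0.8 = 0.02600.

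- 5 years: 1 − exp(−0.1300) = 12.19%, against 12.00%.
- 10 years: 1 − exp(−0.2600) = 22.9%, against 0.8 × (1 − 0.85²) = 22.2%.

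**Assumed 20% deaths.** H = −ln(0.68) / 5 = 0.07713 and h1 = 0.07713 × 0.375 = 0.02892.

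- 5 years: 1 − exp(−0.1446) = 13.47%, against 12.00%.
- 10 years: 1 − exp(−0.2892) = 25.12%, against 0.375 × (1 − 0.68²) = 20.16%.

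| Competing deaths by 5 years | 5 years: censored vs actual | Ratio | 10 years: censored vs actual | Ratio |
|---|---|---|---|---|
| 3% (protocol) | 12.19% vs 12.00% | 1.016 | 22.90% vs 22.20% | 1.031 |
| 10% (assumed) | 12.67% vs 12.00% | 1.056 | 23.74% vs 21.36% | 1.112 |
| 20% (assumed) | 13.47% vs 12.00% | 1.122 | 25.12% vs 20.16% | 1.246 |
| 30% (assumed) | 14.41% vs 12.00% | 1.201 | 26.75% vs 18.96% | 1.411 |
| 40% (assumed) | 15.58% vs 12.00% | 1.298 | 28.73% vs 17.76% | 1.618 |

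The ratios hardly depend on the event rate. With 20% deaths and a 5-year event risk of 5% instead of 12%, they are 1.118 and 1.242.

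**Direction.** The sign does not rest on constant hazards. Cumulative incidence weights the event hazard by the probability of being alive and event-free. The censored calculation weights the same hazard by event-free survival as if no one died, and that weight is never smaller.

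**Cardiovascular endpoint.** The same formulas apply, but F2 is only the deaths outside the definition in section 3.2. The protocol does not split deaths by cause, so no separate figure can be given. For the same total mortality, fewer deaths compete than for the renal endpoint.

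**The case against.** The strongest reply is that section 8.2 builds the score from coefficients and never describes turning it into a probability. Cause-specific coefficients are valid for finding risk factors, and a points score that only orders patients by event hazard carries no absolute risk to overstate. Section 8.3 can also be read as a rule on whose data are included, not on how risk is estimated, and a separate analysis plan might supply the missing step. The first part stands, and it limits the point to absolute risks. The rest does not remove it. The Hosmer-Lemeshow test named in section 8.2 compares predicted with observed probabilities, so some predictions must be absolute, and the protocol names no method for them other than Cox models with follow-up ending at death. If that test counts patients who died event-free as non-events, it might expose over-prediction, but it would not correct it.

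A second reply is that, on the only death rate in the document, the excess is 0.19 percentage points at 5 years. That stands too. Every larger figure above uses mortality that the protocol does not contain.

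A reader might infer that 3% is contradicted elsewhere in the protocol. It is not. The 75-or-older subgroup in section 8.2 is for comparing GFR equations and comes with no death rate. The Background (section 1.1) compares cardiovascular risk with the risk of end-stage renal disease, not death with progression. The 12% comes from two renal cohorts and says nothing about mortality here.

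**Conclusion.** The point holds for absolute risks. As written, sections 8.2 and 8.3 together censor deaths in the models that feed the score. Any 5- or 10-year probability derived from those models alone is too high for the renal endpoint, and too high by less for the cardiovascular endpoint. On the protocol's own 3% and 12% the excess is small: about 1.6% relative at 5 years and 3% at 10 years. It becomes material only if competing mortality is well above 3%, for example about 12% and 25% relative if 20% die by 5 years. These sizes assume constant hazards and, beyond 3%, assumed mortality.

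Three stronger readings are not supported:

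- That the hazard ratios or the list of risk factors are wrong. Cause-specific Cox is appropriate for those.
- That older patients dominate the competing deaths. This is plausible, but the protocol gives no mortality by age; what can be said is that the bias grows with competing mortality.
- That the Background warns of unnecessary referral of frail patients. It says only that patients differ in their need for referral and treatment.

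**What to change.** In section 8.2, keep cause-specific Cox models for identifying risk factors. Add that absolute risks from the score, event curves and calibration at 5 and 10 years will treat death without the event as a competing event. For the cardiovascular endpoint, this means any death outside its definition in section 3.2. Absolute risks can come from cumulative incidence that combines the cause-specific models for the event and for death, or from a Fine-Gray model. Calibration should be checked against Aalen-Johansen estimates. In section 8.3, separate death from withdrawal: withdrawal stays a censoring event, while death counts as a competing event whenever absolute risk is estimated.

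No new data are needed. Section 3.1 already tracks survival through the national information service, and all-cause mortality is a secondary endpoint in section 3.3. The cost is a model for death alongside each event model, or a Fine-Gray model in its place, and slightly lower stated risks. If 3% mortality proves right, the results will barely change; if mortality is higher, the score is protected.
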